## Abstract

**Background:**

Myopia is a growing public health concern among school-going children, with increased screen time and reduced outdoor activities contributing to its early onset and rapid progression. In India, the absence of a standardized, population-based dataset reflecting socio-economic and environmental diversity limits the development of accurate prediction tools. This study aims to design and validate an artificial intelligence (AI)-based model to analyze and predict myopia progression among children aged 6 to 18 years in urban and rural areas.

**Methods:**

This is a prospective, community-based study conducted in two phases across five districts of Bhopal division, India. Phase one involves a cross-sectional survey of approximately 5,000 school children to collect demographic and ocular health data, including visual acuity, refractive error, axial length, corneal parameters, and lifestyle factors. In phase two, a longitudinal cohort comprising 10% of the phase one participants (balanced for existing and non-existing myopia cases) will be followed every 6 months over 2 years. Machine learning algorithms, including linear regression, support vector machines, XGBoost, and deep learning models such as convolutional neural networks, will be trained on this dataset. An AI-based mobile application will be developed to enable field-level prediction and screening.

**Discussion:**

This study will generate the first large-scale Indian dataset on myopia progression among children, incorporating diverse socio-economic backgrounds. The validated AI model and mobile application will support early identification of at-risk children, optimize resource allocation, and inform national screening strategies. By integrating real-time data analytics with field-l.

**Trial registration:**

CTRI/2025/07/091243. Registered on 21/07/2025.

Role of sponsor {5c}	The Indian Council of Medical Research (ICMR), as the funding agency, provides financial support for the conduct of this study under the Investigator-Initiated Research Proposals for Small Extramural Grants scheme. The sponsor has no role in the study design; collection, management, analysis, or interpretation of data; writing of the report; or the decision to submit the report for publication. These responsibilities lie solely with the principal investigator and the research team. The investigators retain full autonomy over the conduct and dissemination of the research

## Introduction

### Background and rationale {6a}

Myopia, or near-sightedness, has emerged as a significant global public health issue, particularly among school-aged children. The rising prevalence of myopia has been linked to increased screen time, reduced outdoor exposure, and behavioral changes following the COVID-19 pandemic. In India, there is a pressing need to address this trend, especially in light of the country’s diverse socio-economic and environmental landscape [1].

Recent global studies have shown that early identification and intervention can slow myopia progression, reducing the risk of severe ocular complications such as retinal detachment, glaucoma, and macular degeneration later in life [2]. Traditional methods of screening and monitoring, however, are often resource-intensive and dependent on access to ophthalmic specialists, which limits large-scale deployment in low-resource settings [3–5].

Artificial intelligence (AI) offers a promising avenue to address these challenges. AI models have demonstrated high accuracy in classifying and predicting ocular diseases based on both imaging and non-imaging datasets. For instance, Foo et al. [6] highlighted the potential of AI in identifying refractive errors using fundus photography, while Li et al. [7] emphasized AI’s role in personalized risk assessment for myopia progression. Additionally, research by Zhang et al. [8] showed that AI algorithms can detect subtle changes in axial length and refractive parameters that may precede clinical diagnosis [9].

Despite these advances, there is a conspicuous lack of standardized Indian datasets to train and validate such models. Most existing models are trained on non-Indian populations and may not account for local variations in genetics, environment, or socio-economic factors. Furthermore, no comprehensive AI-based mobile application currently exists for school-based screening of myopia progression in Indian children.

This study is therefore designed to fill these critical gaps by:Creating a large-scale, representative dataset of ocular and demographic parameters from school-going children across urban and rural areas;Developing and validating AI-based predictive models using both conventional machine learning and deep learning techniques;Integrating the validated model into a mobile application to enable field-level deployment for early detection and intervention.

The initiative aligns with national health priorities by promoting preventive pediatric ophthalmology and leveraging digital health tools to reduce the burden on tertiary care facilities.

### Objectives {7}

#### Primary objective

To develop and validate an artificial intelligence (AI)-based predictive model for assessing myopia progression among school-going children aged 6–18 years, based on demographic, environmental, and ocular health parameters.

#### Secondary objectives

To systematically collect and analyse cross-sectional and longitudinal data on myopia-related risk factors in children from diverse socio-economic backgrounds in urban and rural areas of the Bhopal division.To identify and rank key predictors (e.g., axial length, screen time, parental myopia) contributing to myopia progression using machine learning algorithms.To design and deploy a mobile application embedded with the AI model to facilitate field-level risk prediction and early screening without the need for specialist intervention.To conduct awareness programs aimed at the prevention and early intervention for myopia progression in school children. 

##### ***Hypothesis***

Among school-going children aged 6–18 years, AI-based analysis of ocular and behavioral parameters can accurately predict the risk of myopia progression and serve as a scalable tool for early detection and preventive ophthalmic care in diverse community settings.

### Trial design {8}

This study is designed as a prospective, community-based, observational cohort trial conducted in two sequential phases:Phase 1: A cross-sectional, single-group observational survey of approximately 5,000 school-going children (ages 6–18) across rural and urban regions of the Bhopal division. This phase aims to establish baseline demographic, environmental, and ocular health data.Phase 2: A longitudinal, single-group cohort follow-up involving approximately 500 children (10% of the initial sample), stratified into myopic and non-myopic groups. Participants will be re-evaluated every 6 months over a 24-month period to monitor changes and assess myopia progression.

There is no randomization or allocation to intervention groups, as this is a non-randomized, single-arm exploratory study. The study framework is exploratory, aimed at developing and validating an AI-based risk prediction model rather than comparing clinical interventions. This study is classified as minimal risk, non-interventional observational cohort study. The procedures involved—including visual acuity testing, auto-refraction, axial length measurement, fundus photography, and questionnaire-based data collection—are standard, non-invasive, and routinely performed in school eye screening programs.

## Methods: participants, interventions, and outcomes

### Study setting {9}

This study will be conducted in a community-based school setting across both rural and urban regions of the Bhopal division, located in the state of Madhya Pradesh, India. The Bhopal division comprises five districts: Bhopal, Raisen, Rajgarh, Sehore, and Vidisha.

Data will be collected from government and private schools representing diverse socio-economic backgrounds. Ocular examinations and survey-based assessments will be conducted on-site in schools by field teams comprising ophthalmologists, optometrists, and trained research personnel from All India Institute of Medical Sciences (AIIMS), Bhopal, with technical support from Maulana Azad National Institute of Technology (MANIT), Bhopal.

All study activities will be based in India, and no data collection is planned outside the country.

A complete list of participating schools and study sites can be obtained from the Principal Investigator upon reasonable request. This information is also available in the internal project implementation plan approved by the Institutional Ethics Committee of AIIMS Bhopal.

### Eligibility criteria {10}

#### Inclusion criteria (participants)

School-going children aged 6 to 18 yearsEnrolled in selected government or private schools in urban or rural areas of Bhopal division (Bhopal, Raisen, Rajgarh, Sehore, Vidisha)Children whose parents or legal guardians provide written informed consent and who provide age-appropriate assentWilling to participate in periodic ocular evaluations and follow-up over a 2-year period (for longitudinal phase)Children are considered a vulnerable pediatric population; therefore, inclusion is permitted only with written informed parental/legal guardian consent and age-appropriate child assent in accordance with ICMR National Ethical Guidelines (2017). Additional safeguards, including simplified explanations and the right to withdraw at any time, will be ensured.

#### Exclusion criteria (participants)

Children with a history of ocular trauma, congenital eye anomalies, or prior ocular surgery Children with known systemic conditions affecting ocular health (e.g., diabetes, neurological disorders)Children unwilling or unable to cooperate with ocular examinations or data collection proceduresChildren already enrolled in any other interventional ophthalmic studyChildren who express unwillingness, discomfort, or dissent to participate at any stage of the study, even if parental or guardian consent has been obtained

#### Eligibility criteria for study centers

Schools located within the five districts of the Bhopal divisionInstitutions willing to provide administrative permission and cooperate with data collection activitiesSchools representing diverse socio-economic backgrounds, ensuring representation of urban, rural, and tribal populations

#### Eligibility criteria for study personnel

Ophthalmologists, optometrists, and trained research assistants from AIIMS Bhopal are responsible for clinical evaluation and data collectionAI and data science experts from MANIT Bhopal involved in model development, application programming, and data analysisAll personnel involved in data collection and analysis must have completed ethics and research conduct training and be authorized under the Institutional Ethics Committee protocol As this study involves minors (6–18 years), who constitute a vulnerable population under national and international ethical frameworks, special protections will be implemented Participation will be entirely voluntary. If a child refuses or withdraws assent at any point, their decision will be respected without penalty, irrespective of prior parental consent. No coercion, inducement, or academic influence will be used to encourage participation.

### Who will take informed consent? {26a}

Informed consent will be obtained from the parents or legal guardians of all participating children prior to enrolment in the study. In addition, age-appropriate assent will be obtained from children aged 7 years and above, in accordance with ethical guidelines for paediatric research.Provision of the Participant Information Sheet at least 48–72 h prior to enrolmentConduct of consent procedures by trained research personnel independent of school authorities and not involved in academic evaluation

The process will be coordinated and overseen by trained research staff and ophthalmologists from AIIMS Bhopal. Consent forms will be distributed in the local language (Hindi) as well as in English, and detailed verbal explanations will be provided during parent–teacher meetings or scheduled school visits. The study team will ensure that guardians fully understand the study objectives, procedures, potential risks, and data privacy measures before signing.

For children selected for the longitudinal follow-up cohort, consent will be re-confirmed at each follow-up visit.

All consent and assent documents have been reviewed and approved by the Institutional Human Ethics Committee (IHEC) of AIIMS Bhopal, and signed forms will be securely stored in compliance with data protection regulations.

In addition to written informed consent from parents or legal guardians, age-appropriate assent will be obtained from participating children in accordance with the ICMR National Ethical Guidelines for Biomedical and Health Research Involving Human Participants (2017).

Assent procedures will be tailored to developmental capacity:Children aged 7–11 years**:** A simplified verbal explanation using child-friendly language will be provided, supported by a brief illustrated information sheet in Hindi and English. The study purpose, procedures (vision testing, eye drops, measurements), and the voluntary nature of participation will be explained. Verbal assent will be documented by the investigator.Children aged 12–18 years**:** A written assent form, separate from the parental consent form, will be provided. The form will describe the study objectives, procedures, possible discomfort (e.g., temporary blurring after cycloplegic drops), confidentiality safeguards, and the right to withdraw at any time without academic or medical consequences. Written assent will be obtained and retained in study records.

Children will be given adequate time to ask questions. The explanation will be delivered in a non-coercive environment, without the presence of school authorities influencing the decision.

If a child declines participation or withdraws assent at any stage, their decision will be respected unconditionally, even if parental consent has been granted. Such children will not face any academic disadvantage, and no further study-related procedures will be performed.

To prevent therapeutic misconception, it will be explicitly explained that this is an observational research study and not a therapeutic intervention. Participation does not guarantee medical benefit beyond routine eye screening, and refusal will not affect access to standard clinical care, school services, or academic standing.

### Additional consent provisions for collection and use of participant data and biological specimens {26b}

This study does not involve the collection of biological specimens. However, coded ocular health and demographic data collected during the main study may be used in future ancillary analyses, including algorithm refinement, external validation studies, and related non-commercial academic research projects.

Participants and their legal guardians will be informed of this possibility during the consent process. A specific clause is included in the informed consent form requesting permission for:Future use of de-identified data for related studies approved by the ethics committeeData sharing with collaborating academic institutions under appropriate data sharing agreementsStorage of coded data in a secure, password-protected institutional database for a maximum duration of 10 years

## Interventions

This is a non-interventional, observational cohort study; therefore, no clinical or therapeutic intervention will be administered to participants as part of the trial.

The “intervention” in this study pertains to the development and application of an artificial intelligence (AI)-based predictive model for myopia progression, which will utilize data collected through non-invasive, standard ophthalmic assessments and structured questionnaires. All procedures are observational and diagnostic in nature and include:Visual acuity testing (unaided and best-corrected)Cycloplegic auto-refractionAxial length and corneal thickness measurementsFundus photographyLifestyle and demographic data collection (screen time, outdoor activity, dietary habits, parental myopia history, etc.)

These procedures will be conducted by trained ophthalmologists and optometrists using validated, portable instruments. No drugs, therapeutic regimens, or experimental clinical procedures will be introduced as part of this study.

The AI model and associated mobile application will be applied to collected data retrospectively and prospectively for prediction purposes only, without influencing or altering standard clinical care pathways for participants.

### Explanation for the choice of comparators {6b}

This is an observational cohort study designed to develop and validate an artificial intelligence (AI)-based prediction model for myopia progression. As such, the study does not involve therapeutic or diagnostic interventions requiring active comparators.

However, within the context of AI model development and validation, internal comparisons will be made between:Children with pre-existing myopia and those with no baseline myopia (to identify predictive differences)Multiple machine learning algorithms (e.g., linear regression, support vector machines, XGBoost, deep learning) to determine the most accurate predictive modelAI-based predictions versus clinical assessments and historical progression data during longitudinal follow-up to evaluate predictive accuracy and sensitivity

These internal comparators are essential for optimizing model performance but do not involve assigning participants to treatment or intervention arms. The study is exploratory in nature and does not test the superiority or inferiority of any clinical intervention.

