#### Phase 1: cross-sectional component

A minimum sample size of 1640 children was initially calculated based on:Expected incidence rate of myopia: 3.4% (as per Saxena et al., 2017; PLoS ONE, North India Myopia Study)Confidence level: 95% (*Z* = 1.96)Precision (d): 2.5%

Sample size formula used:

N = Z2 × p × (1 − p)d2N = \frac{Z^2 \times p \times (1—p)}{d^2}N = d2Z2 × p × (1 − p)​ N = (1.96)2 × 0.034 × (1 − 0.034)(0.025)2≈1,484N = \frac{(1.96)^2 \times 0.034 \times (1—0.034)}{(0.025)^2} ≈ 1,484N = (0.025)2(1.96)2 × 0.034 × (1 − 0.034)​≈1,484.

Adjusting for a 10% non-response or attrition rate:

N≈1,640N ≈ 1,640N≈1,640

To increase statistical power and allow for subgroup analysis (by age, gender, urban/rural, socioeconomic status), the sample was scaled up to 5000 participants, ensuring diversity and enabling robust AI model training with stratified data.

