#### Phase 2: longitudinal cohort

A subset of 10% (approx. 500 children) will be selected from Phase 1 using AI-based parameter selection and stratified sampling (equal representation of myopic and non-myopic participants). This sample size is adequate for:Detecting meaningful differences in myopia progression rates (in diopters and axial length)Training and validating AI models using longitudinal data with multiple follow-upsEnsuring sufficient statistical power (> 80%) for machine learning model performance metrics such as AUC, sensitivity, and specificity

Sample size assumptions were determined in consultation with biostatisticians and are justified based on the objectives of developing and validating a predictive AI tool, rather than testing clinical efficacy of an intervention.

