## Data collection and management

### Plans for assessment and collection of outcomes {18a}

#### Baseline and follow-up data collection

Data will be collected in two phases: a cross-sectional baseline assessment (Phase 1) and a longitudinal follow-up (Phase 2). Data collection will be performed on-site in schools across the Bhopal division (Madhya Pradesh, India) by trained field teams from AIIMS Bhopal.Demographic and lifestyle data (questionnaire-based):Instruments: Structured, pre-tested questionnaires administered to parents/guardians and students (as age-appropriate)Variables collected: Age, gender, dietary habits, screen time, near work duration, outdoor activity, family history of myopia, socio-economic statusReliability/Validity: Based on instruments used in previously validated school eye health studies (e.g., AIIMS Delhi NIM Study); pre-tested in a local pilot survey.Ocular assessments (clinical examination):Performed using portable, validated ophthalmic instruments by optometrists and ophthalmologists:Uncorrected Visual Acuity (UCVA) and Best Corrected Visual Acuity (BCVA): Standard Snellen chartCycloplegic Auto-refraction: Handheld autorefractometer with keratometry (validated device)Axial Length and Corneal Thickness: Portable A-scan with pachymeterCorneal Curvature and Refraction Power: Recorded during auto-refractionFundus Photography: Non-mydriatic portable fundus camera

All measurements will be conducted in duplicate where applicable (e.g., axial length) to ensure reliability, and any inconsistencies will be re-checked by a senior clinician on-site.

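### For SER, the baseline examination evidently supplies both the myopic/non-myopic label and the start of the change score, so regression to the mean understates progression mainly in myopes

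*Protocol article*

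**What the plan says.** All places are in the protocol article.

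- **Comparison.** The section on the choice of comparators {6b} names as an internal comparison "Children with pre-existing myopia and those with no baseline myopia (to identify predictive differences"). Subgroup analyses {20b} repeats it as myopic versus non-myopic at enrolment.
- **Selection.** Sample size {14}, Phase 2, takes about 500 children by "stratified sampling (equal representation of myopic and non-myopic participants"). Sequence generation {16a} lists baseline myopia status as a stratification factor.
- **Outcome.** Outcomes {12} defines the primary outcome through change in SER and axial length, summarised as mean change from baseline at each follow-up and stratified by, among other things, baseline refractive status.
- **Timetable.** Participant timeline {13} puts the baseline examination (T0) at months 2–9, cohort selection at month 13 with no eye examination listed, and Visits 1–4 (T1–T4) at months 18, 24, 30 and 36.
- **Measurement.** Section {18a} takes refraction with a "Handheld autorefractometer with keratometry (validated device") and axial length with a separate portable A-scan. It adds that "All measurements will be conducted in duplicate where applicable (e.g., axial length) to ensure reliability". No repeatability figure is given, and no reading is reserved for classification.

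**The concern.** If one SER reading both decides who is labelled myopic and is subtracted from every later reading, its error enters twice. Children labelled myopic have T0 readings that err towards minus on average. Their next reading drifts back, which offsets real progression. Children labelled non-myopic show the reverse.

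Part of the estimated difference between the groups is then a selection artefact. The comparison is meant to show how prediction differs by baseline status, and the same artefact reaches any model trained on T0 refraction to predict change from T0 refraction. A mixed model with a status-by-time term does not remove it if T0 stays among the repeated outcomes. The on-site re-checks and the adjudication panel may catch gross errors, but neither separates the classifying reading from the baseline reading.

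**Working it through.** **Is it the same reading?** The timetable lists one examination before Visit 1, and selection at month 13 comes without another. T0 is the only scheduled source for both roles.

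**Inputs.** From the protocol: the visit months, the example threshold of 0.50 D/year (statistical methods {20a}), and the 3.4% in "Expected incidence rate of myopia: 3.4"%. Assumed, because the protocol gives no values: normal SER with true SD 1.0 D; independent per-visit error SD s of 0.1, 0.15, 0.25 or 0.35 D; 3.4%, 15% or 30% classed as myopic.

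**Formula.** Let X be true SER plus error, with density f and distribution function F, and let children with X ≤ c be labelled myopic. The mean T0 error is −s²f(c)/F(c) in myopes and +s²f(c)/(1−F(c)) in non-myopes. Change from T0 carries the opposite sign. The understatement of the group difference is s²f(c)/[F(c)(1−F(c))].

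**Results for s = 0.25 D.** The SD of X is √(1.0² + 0.25²) = 1.031 D.

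| Classed myopic | f(c) | Understated in myopes | Overstated in non-myopes | Group difference |
|---|---|---|---|---|
| 3.4% | 0.073 | 0.135 D | 0.005 D | 0.139 D |
| 15% | 0.226 | 0.094 D | 0.017 D | 0.111 D |
| 30% | 0.337 | 0.070 D | 0.030 D | 0.100 D |

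A simulation of 2,000,000 children gave 0.141, 0.110 and 0.100 D. I use 0.100–0.141 D below.

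**Other error SDs (group difference, 30% down to 3.4% myopic).** 0.1 D: 0.016–0.023 D. 0.15 D: 0.04–0.05 D. 0.35 D: 0.19–0.27 D.

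**Share of the change.** The shift is a one-off and does not grow with time.
- Visit 1 is 18 − 9 = 9 to 18 − 2 = 16 months after T0. At 0.50 D/year that is 0.375–0.667 D. Share: 0.100/0.667 = 15% to 0.141/0.375 = 38%.
- Visit 4 is 27–34 months after T0, or 1.125–1.417 D. Share: 0.100/1.417 = 7% to 0.141/1.125 = 13%.

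**Linear slope over T0–T4.** With T0 at month 9 the time sum of squares is 3.05 years² and the weight on T0 is −1.2/3.05 = −0.393. With T0 at month 2 they are 4.72 and −1.667/4.72 = −0.353. The slope bias is 0.353 × 0.100 = 0.035 to 0.393 × 0.141 = 0.055 D/year, or 7–11% of 0.50 D/year.

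**Effect on a progression label.** Give both groups the same true 12-month change (assumed mean −0.40 D, SD 0.30 D; s = 0.25 D) and call −0.50 D or worse progression. By simulation, using T0 twice labels 31–36% of myopes and 42–44% of non-myopes as progressors. With an independent baseline reading both are about 41%.

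**Axial length.** With A-scan error independent of refraction error, the simulated mean T0 axial-length error in SER-defined groups was 0.000 mm.

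**The case against.** Several points on the other side stand.

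- **The shared reading is inferred.** A reader might take the protocol to state that children are classified on the T0 refraction. It does not. It gives no cut-off, speaks of pre-existing and baseline myopia, does not rule out a prior diagnosis, and has ophthalmologists verify classifications. The inference rests on the timetable.
- **Only SER is exposed.** A reader might extend the bias to progression in general. Axial length is also a primary measure and comes from another instrument, so the mechanism does not carry over when the errors are independent.
- **The first-visit share is easily overstated.** The nominal 6-month points in Outcomes {12} suggest 0.25 D of change by Visit 1, and so a share of 40–56% (0.100/0.25 to 0.141/0.25). The calendar months give a gap of 9–16 months and do not support that.
- **The 3.4% case is extreme.** The protocol calls 3.4% an incidence, and 0.034 × 5,000 = 170 myopes would not fill a half-cohort of about 250. At 15–30% the shift is 0.10–0.11 D.
- **The error may be small.** Refraction is cycloplegic, and duplicates, if they include refraction, could be averaged.
- **Model details belong to the analysis plan.** Whether T0 enters the mixed model as outcome or covariate may be settled there, and the study is declared exploratory.

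These points limit scope and size. They do not remove the problem from the change-from-baseline summary by baseline status, which the protocol itself fixes.

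**Conclusion.** The point holds for SER. The direction follows from the design once T0 serves both roles: progression is understated mainly in myopes and slightly overstated in non-myopes. The non-myope part is F/(1−F) of the myope part, which is 0.035 at 3.4% myopic and 0.43 at 30%.

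The size rests wholly on the assumed error SD and SER distribution. At an error SD of 0.25 D it matters for early visits and modestly for slopes; at 0.1 D it can be ignored. A reader might conclude that the myopic versus non-myopic contrast is invalid or that change from T0 should be abandoned. The documents do not support that, because the size is unknown, the shift does not grow with follow-up, and axial length offers a largely separate check. This is a cheap improvement to a planned comparison.

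**What to change.** Keep the sampling scheme and the change-from-T0 outcome, and add the following.

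1. For the myopic versus non-myopic SER comparison and the baseline-status subgroup, a sensitivity analysis of the SER slope from T1 to T4, since T1 did not form the groups.
2. In the prediction models, T1–T4 SER change as a sensitivity outcome, with T0 values as predictors.
3. Where duplicate T0 refractions are stored, classify on one and use the other as the change-score baseline.
4. Report SER repeatability, and read the SER contrast alongside axial length.

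**Cost.** Wording and a little analysis, with no new visits or measurements. T1–T4 slopes drop the first 9–16 months. The time sum of squares falls from 3.05–4.72 to 1.25, so the measurement-error part of each child's slope SE rises by √(3.05/1.25) = 1.6 to √(4.72/1.25) = 1.9 times. That is why this should be a sensitivity analysis and not the main estimate. Duplicates from one session share session-level error and remove only part of the bias.
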